#### Exploratory evaluation of the effects of the occupational therapy program (objective 2)

2.7.4

Data collection on the exploratory effects of the occupational therapy program on recovery and RTW will be carried out at baseline, at discharge, and at 6 months follow-up.

##### Effects on recovery

2.7.4.1

To explore the effects of interventions on patient recovery, we will assess depressive and anxiety symptoms, perceived health-related quality of life, occupational balance and personal recovery using the following five questionnaires:

##### Patient health questionnaire-9

2.7.4.2

This questionnaire will be used to assess the intensity of depressive symptoms (52). The PHQ-9 has adequate reliability, excellent discriminant and convergent validity, and a robust structure factor (52, 53).

##### General anxiety disorder

2.7.4.3

This questionnaire will be used to measure the intensity of anxiety symptoms (54). The GAD-7 has excellent sensitivity, specificity, convergent validity and internal consistency, enabling it to be a good screening tool for anxiety symptoms (55, 56).

According to guidelines provided by the Quebec Ministry of Health and Social Services (57) for mental disorder, the GAD-7 and PHQ-9 should be administered when symptoms associated with frequent mental disorders in adults are present.

##### Short-Form 12

2.7.4.4

The Short-Form 12 (SF-12) will be used to measure self-perceived health-related quality of life and includes eight domains assessing physical and mental health (58, 59). The SF-12 is an adapted version of the SF-36, whose validity, test-retest reliability and responsiveness to change have been repeatedly demonstrated in the literature (60, 61). This test has also been validated to assess health-related quality of life in cohorts with mental health conditions (62).

##### Occupational Balance Questionnaire

2.7.4.5

The Occupational Balance Questionnaire will be used to document the person’s level of life balance, i.e., the extent to which a person achieves a good quantity and variation of occupations. The score of this questionnaire is strongly correlated with perceived health (63, 64). The original version demonstrates a good internal consistency, and satisfactory test-retest reliability (63). The French-language version of this questionnaire demonstrated good internal consistency and satisfactory test-retest reliability in Quebec (64).

##### Brief INSPIRE-O

2.7.4.6

The Brief INSPIRE-O is an adapted version of the Brief INSPIRE designed to assess personal recovery outcomes. It is a five-item self-reported outcome measure based on the CHIME framework for recovery (65). Each item is meant to assess one of the five processes described by the CHIME framework: Connectedness, Hope and optimism, Identity, Meaning and purpose, and Empowerment (66, 67). Its validation demonstrated good scalability, satisfactory internal consistency, and moderate test-retest reliability (65).

##### Effects on RTW

2.7.4.7

Effects on RTW will be assessed by documenting work status at discharge and at six months follow up using a validated grid (68), job type, and self-reported duration of absence from work. In addition, two questionnaires will be used to document perceived RTW self-efficacy and work functioning at baseline, at discharge and at six month follow up.

##### RTW self-efficacy questionnaire

2.7.4.8

The RTW self-efficacy questionnaire (RTW-SE) will be used to evaluate RTW self-efficacy. The original English version of the RTW-SE has excellent internal reliability, adequate test-retest reliability and good sensitivity to change, and is identified in the literature as having predictive validity for RTW (69, 70). The French-language version was translated in a two-stage process by the Institut de recherche Robert-Sauvé en santé et sécurité du travail (71).

##### Work Role Functioning Questionnaire

2.7.4.9

We will use the Work Role Functioning Questionnaire (WRFQ) to evaluate work functioning, the extent to which an induvial feels able to meet the physical, mental, and social demands of the job (72, 73) The Canadian French version of the WRFQ has good content validity, very good internal consistency for all items except the social demands scale, and good construct validity (72, 74).

### Analysis

2.8

The Framework Method will be used to analyze the data associated with each objective. It is an analytical method suitable for multiple case studies, mixed research designs, and for managing large amounts of data (75). The seven steps of the method will be used for each case: 1) transcription of the data, 2) familiarization with the data, 3) coding, 4) development of an analytical framework, 5) application of the analytical framework, 6) classification of the data in the analytical matrix, and 7) interpretation of the data. All qualitative and quantitative data will be integrated into the NVivo 14 analysis software to create the results matrix. To contextualize the data for each case, the contextual data will be analyzed using the CFIR domains and constructs to create a portrait of each study site (37). The results of the analysis will be discussed with the research team members.

#### Objective 1 - acceptability assessment

2.8.1

Data collected for pre-implementation, during implementation and post-implementation assessment will be analyzed separately using a combined deductive and inductive thematic analysis approach (75, 76). Data will be organized to document each of the TFA domains. Two members of the research team will iteratively cross-code the data, reviewing the analyses performed for each case on an alternating basis to improve the intersubjective traceability of the coding.

Quantitative data collected using the TFA questionnaire will be analyzed using descriptive statistics, and differences between pre- and post-implementation results will be assessed with a paired t-test (or Wilcoxon signed ranks test if data are not normally distributed) using SPSS 29 software.

The results of the quantitative and qualitative analyses of acceptability will be reported into a joint display table to compare them for each of the components of the TFA model and will consider the different levels of analysis, i.e. acceptability at the U-FMG level, for the different professionals and for the patients (77). The results matrices produced for each case will then be compared (cross-case analysis) to analyze the influence of context variables on levels of acceptability pre-, during and post-implementation of interventions (38).

#### Objective 2 - exploratory evaluation of effects

2.8.2

Quantitative data on recovery and RTW will first be analyzed for each case independently, to document the effects produced by the intervention program by comparing the results obtained at baseline, discharge, and six months after the end of the interventions. Depending on the nature of the data, either parametric (ANOVA) or non-parametric (Friedman test) repeated measures statistics will be used. Analysis evaluating the differences between the results obtained for patients from the three U-FMGs will also be carried out using SPSS 29 software.

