### Study design

2.2

A mixed methods multiple case study research design will be used (38). Case study is a naturalistic research approach that allows to explain and explore a phenomenon in its context (38), in this case, the implementation of an occupational therapy program in a new environment that is the FMG. This research approach will provide an in-depth understanding of the perspective of those who deliver the intervention in an FMG context, as well as those who receive it. It will also document the elements of the intervention and the context on which action must be taken to optimize its effects (39).

To achieve an in-depth understanding of the acceptability and explore the effects of each case, the present study will use a mixed methods case study design with a convergent design (40). For the acceptability assessment objective, the quantitative and qualitative components of this study will document the evolution of acceptability from the pre-implementation phase to the post-implementation phase and evaluate the similarities and differences between the perceptions of the various stakeholders, including health care professionals, insurers, employers, union representative.

To explore the effects of the occupational therapy program, a pre-test/post-test research design without a control group will be used. Quantitative data will be collected to measure the changes produced by the intervention on the patient’s recovery and RTW outcomes. The qualitative component will explore the patient’s perceived outcomes of the program in more depth.

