**WHEN AND HOW MUCH (number of sessions, duration, intensity)**	Patients will be referred to the occupational therapist as soon as possible to prevent sick leave or ensure appropriate RTW coordinator support and referrals to external resources. Interventions may vary depending on whether the patient has access or not to occupational therapy services in the private system. If occupational rehabilitation services are offered by the U-FMG, we expect a one-hour appointment per week for two to up-to 16 weeks, depending on the patient's health and needs, as well as the characteristics of his or her job and work environment.
**TAILORING (personnalization)**	The intervention will be tailored to the patients’ needs and insurance coverage. It may therefore vary in terms of intensity of follow-up and duration. Patients will be referred to private services when they have access to them, and the occupational therapist will act primarily as a RTW coordinator in this situation. For patients who do not have access to private services, the intensity of interventions will be greater to provide psychosocial support and work rehabilitation services RTW.
**HOW WELL (planned)**	Occupational therapists will receive training before the study begins and mentorship will be offered to ensure that the interventions offered are delivered in respect of the recovery-oriented approach and the therapeutic RTW approach for CMD. U-FMG teams will also receive training on the role of the occupational therapist.

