### Patient recruitment strategy

2.6

For recruitment purposes, physicians and SNPs will be asked to identify patients with a diagnosis of CMD for whom a decision of sick leave has been made or may be considered. These patients will be referred to the occupational therapist. If they agree to participate in the study, a member of the research team will meet them to verify their eligibility, and to obtain their informed consent to participate in the study. Recruitment will take place over 12 months in each U-FMG.

To be eligible patients must be: 1) consulting a family physician or a SNP for a CMD, 2) referred to the occupational therapist for a new episode of sick leave or wish to prevent a sick leave, and 3) able to speak, read, and understand French or English. In this study, CMDs include depressive disorders, anxiety disorders, obsessive-compulsive disorder, and trauma- or stress-related disorders, including adjustment disorders (49). Patients will not be eligible if they: 1) have a diagnosis of a severe mental disorder limiting work integration or participation and 2) require or receive services from a specialized mental health care team.

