### Potential challenges and strategies to mitigate the risk

3.1

Some challenges and limitations to this study must be acknowledged. First, it will be important to have the collaboration of the family physicians and SNPs to refer patients to the new occupational therapists integrating their team. It will also be important that they have a good understanding of the occupational therapist’s role. Training and close monitoring of these factors in the U-FMGs will be important. On the other hand, it is possible that the occupational therapist will receive too many referrals. Should this occur, a waiting list will be created. It is expected that the intervention will be delivered in a timely matter to the participants and problem-solving strategies will be used to identify how to improve appropriate referrals and avoid delays in treatment. The participatory research approach will support the engagement of U-FMG managers and professionals, patient partners and the research team in the problem-solving process. Furthermore, given that the U-FMGs (cases) were selected, in large part, due to their interest towards improving CMD care and services, the level of acceptability of those clinics could potentially be higher than those of other FMGs. The use of a mixed methods multiple case study will provide an in-depth understanding of these three cases from three different regions and a better understanding of how contextual factors influence the acceptability of this type of intervention Transferability may be limited since the project will be conducted in the province of Quebec. The results will be transferable to countries with healthcare coverage similar to Canada's, i.e. universal healthcare coverage. Given the exploratory nature of the intervention effects, the generalizability of this part of the results will be limited. Finally, while beyond the scope of this study, it will be relevant and important to assess the cost-effectiveness of this intervention to determine if scaling-up should be promoted and how it can support changes to insurance coverage and wider provision of public services.

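### The repeated-measures ANOVA and Friedman test named for objective 2 use only patients with all three assessments, which costs precision and can bias the change estimates unless loss is completely random

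*Protocol article*

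**What the plan says.** Section 2.7.4 of the protocol article sets three assessments for the exploratory effects; data collection "will be carried out at baseline, at discharge, and at 6 months follow-up". Section 2.8.2 names the methods: "Depending on the nature of the data, either parametric (ANOVA) or non-parametric (Friedman test) repeated measures statistics will be used". It also fixes the level of analysis: "Quantitative data on recovery and RTW will first be analyzed for each case independently". The comparison of sites is a further step: "Analysis evaluating the differences between the results obtained for patients from the three U-FMGs will also be carried out using SPSS 29 software".

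Three other statements bear on the point. Section 2.2 says that "a pre-test/post-test research design without a control group will be used". Table 2, for patients whose rehabilitation is given at the clinic, says "we expect a one-hour appointment per week for two to up-to 16 weeks", so the last assessment falls roughly 6.5 to 10 months after the start. Section 3.1 concedes: "Given the exploratory nature of the intervention effects, the generalizability of this part of the results will be limited".

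For objective 2 the article gives no number of patients, expected attrition, mixed model or imputation. On recruitment it gives only a time window: "Recruitment will take place over 12 months in each U-FMG".

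**The concern.** The criticism is of a method that the article states. Classical repeated-measures ANOVA works on complete rows, and the Friedman test ranks three values within each patient. Neither can use a patient with one value absent, so choosing between them does not help. A patient seen at baseline and discharge but not six months later contributes nothing, although the baseline-discharge change was fully observed.

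Two things are at stake. Information already collected is thrown away, and because each site is analysed separately first, the loss falls on single-site samples. Also, if the patients who return at six months differ from those who do not, the reported change describes the retained patients only. There is no control group, so the within-patient change is the entire effect estimate. The article says that promising results would lead to an experimental study (section 3) and describes this study as the first step towards a randomized trial (section 4).

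**Working it through.** The plan gives no figure to reproduce. Everything below rests on assumed inputs and shows a range.

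**1. Patients kept by complete-case analysis.** Let d1 and d2 be the proportions missing at discharge and at six months. The number kept is N(1 - d1)(1 - d2) if the two are independent, and N(1 - d2) if everyone missing at discharge is also missing at six months. With an assumed N = 60 per site:

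| d1 / d2 | Independent | Monotone |
|---|---|---|
| 5% / 10% | 51 | 54 |
| 10% / 20% | 43 | 48 |
| 15% / 30% | 36 | 42 |
| 20% / 40% | 29 | 36 |

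**2. Precision when only the six-month value is missing.** Assume unit SD, a baseline-discharge correlation of 0.5, N = 90 and 29% missing at random. The variance of one patient's change is 2(1 - 0.5) = 1.
- All patients seen at both visits: SE = sqrt(1/90) = 0.105.
- Complete cases only: SE = sqrt(1/(0.71 × 90)) = sqrt(1/63.9) = 0.125.
- Ratio: 1/sqrt(0.71) = 1.19.

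For N = 30 the same formulas give 0.183 and 0.217.

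**3. Bias, by simulation.** Assumptions: N = 90, 4,000 replicates, correlations 0.5 (baseline-discharge), 0.4 (baseline-six months) and 0.6 (discharge-six months), true changes of -0.50 and -0.70 SD, and 29% missing at six months. One-tailed loss follows a logistic model in the discharge score, higher meaning worse. The likelihood analysis is the one behind an unstructured mixed model.

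| Loss at six months | Baseline-discharge, complete case | Baseline-discharge, likelihood |
|---|---|---|
| Completely random (slope 0) | -0.50 | -0.50 |
| Both extremes of the discharge score | -0.50 | -0.50 |
| Worse discharge score, slope 0.5 | -0.57 | -0.50 |
| Worse discharge score, slope 1 | -0.62 | -0.50 |
| Worse discharge score, slope 1.5 | -0.66 | -0.50 |

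At slope 1 the overstatement is (0.621 - 0.500)/0.500 = 24%. The SE for this contrast was 0.122 against 0.106 at slope 1 (ratio 1.15) and 0.127 against 0.107 under random loss (ratio 1.19).

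The six-month change at slope 1 was -0.725 for complete cases and -0.699 for likelihood: 0.026/0.699 = 3.7%. The harm falls mainly on the baseline-discharge contrast.

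**4. Where the alternative does not help.** With loss driven by the unseen six-month score itself, the six-month change (true -0.70) was -0.85 for complete cases and -0.86 for likelihood. The baseline-discharge change was -0.55 and -0.50 respectively.

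**5. A second setting, with discharge values also missing.** Assumptions: N = 60, SD 5, means 14/9/8, correlation 0.5 or 0.7, and 10-15% missing at discharge with 20-30% at six months.
- Missing at random: complete-case bias was 0.12 to 0.31 points in absolute value (0.02 to 0.06 SD); likelihood bias was at most 0.03.
- Missing not at random: six-month bias was -0.26 to -0.57 for complete cases and -0.41 to -0.89 for likelihood.
- In all scenarios the complete-case SE was 5-22% larger.

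**The case against.** The strongest reply is that neither attrition nor its pattern is known. With complete follow-up nothing is lost, and with completely random loss nothing is biased. Even selective loss need not bias the mean: if the least and the most improved patients both drop out, the errors can cancel, as step 3 shows. This stands. A reader might infer that the planned tests will give biased results; the documents support only that they can.

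The 24% is also one scenario, chosen from one tail and for one contrast, and should not be read as a forecast. Nor should complete cases be judged against full data. With 15% and 25% missing independently, 0.85 × 0.75 = 0.64 of patients are complete and the SE rises by 1/sqrt(0.6375) = 1.25, but no method recovers all of that. The fair comparison is with a likelihood analysis of the same data.

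The mixed model has its own limit: it is valid under missing at random, and in step 5 it did worse than complete cases when that failed. This must be stated with the proposal.

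Two further readings go too far. Calling the sites small has no support, since no sample size is given. Faulting the Friedman test because it cannot compare sites or adjust for covariates is largely preference: section 2.8.2 plans the site comparison as a separate analysis and plans no covariate adjustment.

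Finally, imputation before the ANOVA could be specified in a full protocol or analysis plan that is not shown. Its absence from an article is no fault. The point concerns the tests that are named, which in standard form use complete triples.

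**Conclusion.** The point holds in a limited form. The named tests discard patients with any one missing assessment, including their observed baseline-discharge change. Precision is lost whenever data are missing. Bias is possible, but not certain, when loss is not completely at random.

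Under the assumed 90 patients and 29% missing at six months, the baseline-discharge change ranged from unbiased to about 24% overstated, or more with stronger selection, with a standard error about 15-19% larger than necessary. At the 24% scenario the six-month change moved by under 4%. The second assumed setting gave smaller biases under missing at random. The true size cannot be derived from the article.

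The exploratory, uncontrolled status of objective 2 limits the severity, and the missing control group threatens any effect claim more than this does. What remains is a real gain in precision, and a baseline-discharge change that loss at six months cannot distort.

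**What to change.** In section 2.8.2, for each continuous scale score:

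- Replace the repeated-measures ANOVA with a linear mixed model (SPSS 29 MIXED, REML, unstructured covariance over the three visits) fitted to all available observations. Include time in the single-site analyses, and time, site and site × time in the cross-site analysis.
- Report mean change with a 95% confidence interval for baseline-discharge and baseline-six months.
- For skewed scores, use robust or bootstrap standard errors instead of switching to the Friedman test.
- State that the model assumes missing at random, and compare the baseline characteristics of responders and non-responders at each later assessment.
- Name a different model for categorical outcomes such as work status, which a linear mixed model does not suit.

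The cost is a change of analysis wording. The data and assessments stay the same. The mixed-model procedure is part of the named software; that is general software knowledge, not something the article states.

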### Trustworthiness

2.9

Strategies will be used by our team to ensure the trustworthiness of our findings. The study will allow the research team to have a prolonged engagement with each site helping them to achieve a nuanced insight of the phenomenon under study. A research journal will be kept by the research coordinator and the occupational therapists providing the intervention to document factors influencing the acceptability and implementation of the intervention. As described previously, we will use triangulation to collect various sources of data from multiple stakeholders. We will also thoroughly document the research process and decisions made by the research team and the implementation support committees of each research site. Debriefing with the research team will be performed regularly throughout the study. In-person group meetings will be conducted at the time of final data analysis for results validation. Results will also be presented at each research site to improve confirmability of findings. Transferability will be ensured by the thorough description of the research context, participants and also by collecting data on the perspectives of stakeholders in regard to the possible implementation of the program in other U-FMGs and FMGs in the province of Quebec.

